### Physical activity

To monitor the physical activity levels among elderly, the Step Watch 3 Activity Monitor (SAM) is used. SAM is an ankle-worn pedometer and contains a custom sensor that uses a combination of acceleration, position, and timing to detect steps [﻿77﻿]. SAM is calibrated based on each participants height and gait pattern. The SAM has been deemed valid and reliable for monitoring step count at different walking speeds, especially for slow speeds [60, 61, ﻿78﻿], which is highly relevant for the current study. The step count is recorded over five consecutive days [﻿79﻿] with participants wearing the SAM during daytime. An activity log is provided so the participants can fill in non-wear pedometer periods.

In addition to the recorded step count, participants also complete a self-reported questionnaire: International Physical Activity Questionnaire, Elderly, Short Form (IPAQ-elderly). It contains four questions involving time spent 1) sedentary, 2) walking, 3) with moderate physical activities, and 4) with vigorous physical activities during the previous 7 days. IPAQ-elderly is a valid and reliable questionnaire [﻿62﻿, 80]. As the questionnaire does not exist in a Danish version, the Swedish version is used. Sweden and Denmark are both Scandinavian countries with similarities regarding the elderly population, culture, healthcare system, and language [81–83]. As recommended, the test-person receives guidance from an experienced tester when answering the questionnaire [﻿84﻿].

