## Background

Accidental falls are common in the elderly population [1] with increased risk of falls with increased age and level of fragility [2–5]. Among home-dwelling older adults (≥65 years), 33% will have at least one fall per year [2, 6, 7] with higher prevalence as the age increases (i.e., 40% over 80 yrs) [8–10]. Such accidents cause injuries, fear, and reduced quality of life [11, 12] along with increased morbidity (e.g., higher risk of institutionalization and hospitalization) and mortality [11–13]. Moreover, falls are the most prevalent cause for injury-related deaths among older adults ≥65 years [14]. It is estimated that up to 0.20% of the gross domestic production and 0.85–1.50% of the health care costs are related to fall incidences [15]. With a rapidly growing proportion of individuals over 65 years, this group is projected to represent 15.6% of the world’s population by 2050 [16] constituting both a present and future societal challenge. In summary, the burden of accidental falls among older adults on the individual, family, community, and society is tremendous [2]. Therefore, fall prevention in this population is considered a point of focus in relation to public health globally [17].

Various risk factors, such as muscle weakness, history of falls polypharmacy, gait, and balance deficits increase fall risk [18–20], indicating that both clinical data and technical assessments are important for screening a multifactorial problem such as fall risk [6, 21]. An embedded definition by Tinetti and colleagues (1998) states a fall as: “*an event which results in a person coming to rest unintentionally on the ground or lower level, not as a result of a major intrinsic event, such as stroke, or overwhelming hazard*” [11]. Accidental falls are often classified into intrinsic (e.g. non-accidental causes such as history of falls, age, gender, solitary lifestyle, fear of falling, nutritional deficiencies, cognitive disorders, attenuated vision, balance and gait impairment, and foot problems), extrinsic (e.g. polypharmacy) and environmental (e.g. lighting, footwear, and bumpy and slippery surface areas) risk factors [18, 19, 22, 23]. Intrinsic risk factors such as poor balance or gait impairment are particularly common causes to ‘slip and trip’ which may result in accidental falls among older adults [9, 22, 24, 25].

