The size of the study population was estimated based on previous studies on objective measures of physical activity (exposure) and self-reported fall incidence by telephone interview (outcome). Various Danish studies and cohorts have used diurnal recordings of physical activity with accelerometers [53, 54], including the NOMAD study and the DPhacto cohort. Depending on the specific aim of studies from these cohorts, the number of included participants varies from *n* = 198 [﻿55﻿], *n* = 457 [﻿56﻿] and up to *n* = 657 [﻿57﻿]. Among community dwelling older adults aged ≥65 years, approximately one third falls at least once a year [2, 6, 7]. The sample size in studies on fall incidence using telephone interviews have used samples of *n* = 326 and *n* = 331 participants [﻿58﻿, 59]. The assumed number of participants needed at various stages in the recruitment flow from the first contact to complete follow-up data are inspired and modified from the DPhacto protocol paper [﻿53﻿] and are illustrated in Fig. 1. Thus, based on previous studies on both the exposure and outcome, it is estimated that a sample of 600 participants is needed for baseline and 450 participants with complete baseline and follow-up data.

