**Fig. 2 Fig2:**
[figure not shown]
The NOCfao study timeline

**Table 2 Tab2:** Assessment overview of the timing and content in the NOCfao study

Domain	Type of Assessment	Notes	BL	DM	FU		Origin
Demographic data	Age	Self-reported	x				
	Gender	Self-reported	x				
	Height	Measured in centimeters	x				
	Weight	Digitally measured on forceplate	x				
	Marital status	Self-reported	x				
	Type of dwelling	Self-reported	x				
	Use of mobility aids	Self-reported	x				
	Use of homecare	Self-reported	x				
Health information	Chronic diseases	Self-reported	x				
	Number of prescribed medications	Self-reported	x				
	Fluid intake	Self-reported	x				
Physical activity	Objectively measured physical activity	Pedometer (Stepwatch3), Repeatedly over 5 days		x			[60, 61]
	Self-reported physical activity	IPAQ-elderly	x				[﻿62﻿]
Pain sensory profile	Muscle tissue	Pressure Pain Threshold	x				[﻿63﻿]
	Severity and duration of pain	Self-reported obtained by NRS	x				[﻿64﻿, 65]
	Location of pain	Body chart	x				[﻿66﻿]
Physical tests	Walking speed	10 m walking test	x				[﻿67﻿, 68]
	Muscle strengths in lower extremities	30-s sit-to-stand	x				[﻿69﻿]
	Muscle strengths in upper extremities	Seehan digital Hand grip dynamometer	x				[﻿70﻿, 71]
	Balance	Force plate measures	x				[﻿72﻿]
		Mini-BESTest	x				[﻿73﻿, 74]
Psychological factors	Anxiety of falling	Falls efficacy scale - International	x				[﻿75﻿]
Fall incidence	Fall incidence and fall circumstance	Phone-interview on a monthly basis. Prospective 1 year			x		[﻿76﻿]
	Fall history	Self-reported one-year history of falls	x				

Notes: *BL*: Baseline; *DM*: Diurnal measurements; *FU*: Follow-up

In order to collect baseline data, individuals included in the study are asked to:
Complete three questionnaires to describe: the characteristics of the cohort, health information, history of falls, anxiety of falling, and self-reported PAPerform physical tests measuring strength in the upper and lower extremities, balance, and walking speedParticipate in assessment of pain sensitivity by recordings of pressure pain threshold (PPT)Wear an ankle mounted pedometer (Stepwatch 3) for measuring activity for five consecutive days

Baseline data, application and use of the activity monitor are supervised by physiotherapy students under the guidance of an experienced physiotherapist. The students receive training through several workshops to ensure high reliability in the test procedure.

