To monitor fall incidences, the project manager or students contact participants on a monthly basis by phone throughout the year after recruitment. The numbers of fall incidences during the previous 1 or 2 months are collected, and the circumstances surrounding the falls are registered. The baseline data will be collected between the autumn of 2016 and the end of autumn 2019, and follow-up data between the autumn of 2017 and 2020 (see Table 2).

Data in paper form collected at baseline are physically stored in locked cabinets in a room with an electronic lock complying with the Danish Data Protecting Agency and Institutions guidelines. All data will be entered electronically and stored in a secured database.

In terms of confidentiality data will be identified by a coded ID number. All records that contain names or other personal identifiers, such as locator forms and informed consent forms, will be stored separately from study records identified by code number.

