### Fall incidence

Fall history of the participants are measured retrospectively as a 12-month recall of falls at baseline. Prospective falls are ascertained over a 12-month period by monthly phone calls with the purpose of determining both the number of falls, why the fall occurred, where it occurred, and when during the day the fall incidence happened. Falls are listed as number of falls and expressed in groups: fallers, non-fallers and multiple fallers along with fall rate per person in a year. This is in accordance with international recommendations [﻿84﻿].

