## Discussion

It is the authors’ belief that the NOCfao study will provide a distinctive and clinically applicable method to fall risk assessment for community-dwelling older adults. The main aim of this paper is to describe the methods and foundation of the NOCfao study. If the main study hypotheses of this prospective, observational cohort study are accepted, this will highlight the importance of physical activity and impaired postural stability in relation to falls among community-dwelling older adults. Applying this knowledge in this population may contribute to a reduction in the number of falls, which will benefit the community-dwelling older adults, the family, the community, and reduce the societal costs.

This study encompasses various important strengths to supplement to the present-day understanding on the association between physical activity and impaired postural stability and the number of falls among community-dwelling older adults. For objective measures of step monitoring, the SAM is small and light-weighted and is reported to be well-tolerated by older patients [78]. It does not interfere with the community-dwelling older adults’ daily life, nor does it provide any information to the participants that may introduce sudden changes in motivation and thereby the level of PA. This is therefore expected to reduce the risk of under- or overestimation. The measures of PA will contain several days of recordings, which will advance the authentic representation of PA in community-dwelling older adults. Lastly, the objective measures using SAM have been shown to be valid and reliable in populations of community-dwelling older adults [60, 78], but SAM has not yet been introduced in cohorts on fall risk assessment. The prospective monthly follow-up on number of falls and the circumstances they occur in, reduces the risk of recall bias and allows for stratified analyses on specific type of fall incidence.

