### Limitations and methodological considerations

We recognize that the NOCfao study contains limitations. First, the objective measures of PA are represented only by the recorded step count and the walking speed obtained from the 10 m walking test. Even though these two methods are valid, reliable, and associated with fall status [38, 67], they only portray a narrow aspect of PA. Therefore, a self-reported questionnaire (i.e. IPAQ-elderly) encompassing information on time spent 1) sedentary, 2) walking, 3) with moderate physical activities, and 4) with vigorous physical activities during the last 7 days are also applied. Nevertheless, these self-reported measures of PA can be subject to bias, given their link to elements such as community-dwelling older adults’ tendency to overestimate or underestimate the level of PA, recall errors, misunderstanding the question format, social desirability in front of an interviewer, and lower educational level [84, 99–101]. The interaction remains uncertain with respect to the relationship between PA and the prospective one-year follow-up on falls. Further, the recruitment process may initiate a selection bias among the community-dwelling older adults included in this study. In other words, the participating community-dwelling older adults included in this study may be resourceful and motivated in terms of their ability to locate and respond to the advertising platforms, and perform better at a baseline test as well as wearing SAM, keeping a diary, and being willing to provide information throughout a 12-month period. An important non-physical risk factor, executive function [102] is currently not included in the present protocol and should be addressed in the future studies.

This study will add to the present-day understanding of the association between PA and impaired postural stability and the number of falls among community-dwelling older adults, providing valid and reliable information on the relationship and its significance among community-dwelling older adults.

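### The main exposure is one five-day step count taken at any time of year, and season of wear is neither a listed variable nor a stated limitation

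*Protocol article*

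**What the plan says.** The first main study question in the protocol article (Aims) is whether physical activity is associated with fall episodes. The sample-size section names objectively measured activity as the exposure. Under Physical activity, "The step count is recorded over five consecutive days", with daytime wear. Under Data collection, participants are asked to "Wear an ankle mounted pedometer (Stepwatch 3) for measuring activity for five consecutive days", and Table 2 marks the recording once, at the diurnal-measurement stage, with no repeat during follow-up.

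On timing, "The baseline data will be collected between the autumn of 2016 and the end of autumn 2019". On the outcome, "Prospective falls are ascertained over a 12-month period by monthly phone calls".

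The statistical section lists the factors to be related to falls: physical activity, postural sway, psychological factors, fall incidence, socio-demographic data, health information, physical tests and pain profile. It allows for adjustment in general terms. Date or season of wear is not on the list.

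The Discussion presents the recording as a strength: "The measures of PA will contain several days of recordings, which will advance the authentic representation of PA". The limitations section says of step count and walking speed that "they only portray a narrow aspect of PA", and discusses self-report bias and selection. It does not mention when in the year the steps were counted.

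**The concern.** One participant's exposure may be a winter week and another's a summer week, while both outcomes are a full year of falls. If older adults walk less in some months, two people with the same usual activity will record different step counts only because of when they were tested. That is measurement error in the variable on which the first study question rests.

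Three things are at stake: a weaker estimated association, some loss of power, and a harder-to-use step level in the planned prediction tool, since the same person could score differently by month of testing. The Background also raises a possible u-shaped relation between activity and falls. Curvature is more sensitive to exposure error than a straight line.

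Five consecutive days also hold a varying number of weekend days, depending on the start day. The same question applies there on a much smaller scale.

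**Working it through.** The article gives no step-count SD, seasonal swing, weekday difference, effect size or power, so there is no stated figure to reproduce. Everything below except the design facts is an assumption, shown over a range.

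**1. Season as the only error.** Let measured steps = usual steps × (1 + A·cos(time of year)), with testing spread evenly over the year and usual steps log-normal.

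- Between-person log variance: v = ln(1 + CV²), so ln(1.16) = 0.1484 at CV 40% and ln(1.25) = 0.2231 at CV 50%.
- Seasonal log variance: s² = 2·Σ b^(2k)/k², with b = (1 − √(1 − A²))/A. This is close to A²/2.
- Attenuation factor for the log-step slope: λ = v/(v + s²).

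| Swing A | s² | λ at CV 40% | λ at CV 50% | Slope lost |
|---|---|---|---|---|
| ±10% | 0.0050 | 0.967 | 0.978 | 2-3% |
| ±20% | 0.0205 | 0.879 | 0.916 | 8-12% |
| ±30% | 0.0474 | 0.758 | 0.825 | 18-24% |

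If activity entered as a quadratic, curvature would shrink by roughly λ². At ±20% that is a loss of about 16% (1 − 0.916²) to 23% (1 − 0.879²). This is approximate, because the λ² rule assumes normal error.

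**2. Season on top of day-to-day variation.** Set the between-person SD to 1 and assume a day-to-day SD of 0.7 averaged over five days, with seasonal half-amplitude a in SD units: λ = 1/(1 + 0.49/5 + a²/2).

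- No season: 1/1.098 = 0.911.
- a = 0.1, 0.2, 0.3, 0.5: 0.907, 0.894, 0.875, 0.818.
- Further loss due to season, 1 − 1.098/(1.098 + a²/2): 0.5%, 1.8%, 3.9%, 10.2%.

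The two calculations agree. The log SD is √0.1484 = 0.385 or √0.2231 = 0.472, so a = 0.5 is a swing of about ±19% to ±24%, and 10.2% sits beside the 8-12% in the table.

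**3. Power, for scale only.** Take 450 completers (the article's figure), one third falling (the article's figure), two-sided 5%, and an assumed true risk ratio of 1.5 across a median split (26.7% against 40.0%). With the ratio shrunk to 1.5^√λ, power is 85.3% at λ = 1, 81.5% at λ = 0.90 (ratio 1.469) and 76.9% at λ = 0.80 (ratio 1.437).

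**4. Weekday mix.** A Monday start gives 0 weekend days, Tuesday or Sunday gives 1, and Wednesday to Saturday gives 2. If weekend steps are 20% lower, the true weekly mean is (5 + 2 × 0.8)/7 = 0.943 of the weekday mean. The five-day mean is then off by 1/0.943 − 1 = +6.1% with no weekend day, 0.96/0.943 − 1 = +1.8% with one, and 0.92/0.943 − 1 = −2.4% with two. With equally frequent Monday-to-Friday starts, the log variance of this error is about 0.0011. The slope loss is 0.0011/(0.1484 + 0.0011) ≈ 0.7% at CV 40% and 0.0011/(0.2231 + 0.0011) ≈ 0.5% at CV 50%.

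**The case against.** The strongest reply is that this is an analysis matter. Covariates are commonly left to a statistical analysis plan, which is not shown here, and the article does foresee adjustment. That stands in part: the missing covariate is not in itself an error, and the design does not prevent the remedy. What remains is in the article itself. It describes one short recording with no control of season, presents it as a strength, and has a limitations section that is silent on timing.

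The size is also unknown. At ±10% the loss is 2-3%, which few would act on. The five-day length carries a citation that cannot be checked here. An even spread of testing over the year is assumed; the text gives only the start and end of the baseline period.

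Several stronger readings are tempting but unsupported:

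- **That participants are placed in the wrong activity group.** The article defines groups by falls, not by activity, and gives no step cut-off. Misclassification would arise only if steps were later categorised. Even then, day-to-day variation alone would cause much of it: with an assumed daily CV of 30-50%, 22-38% are in the wrong quartile before any season is added, and a ±20% swing adds about 5-11 percentage points.
- **That winter-tested participants who leave early bias the result.** This needs seasonal steps, seasonal fall risk and early loss to act together, and none is quantified. The Background lists "lighting, footwear, and bumpy and slippery surface areas" as environmental risk factors and says nothing about months.
- **That the article equates five days with habitual activity for a year.** It does not say so. It relates the count to one-year falls and makes the more modest claim quoted from the Discussion.
- **That weekday mix is a comparable problem.** It is not; the expected effect is under 1%.

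**Conclusion.** The point holds as a design limitation of modest weight that can be largely removed. It is not a contradiction or a wrong figure. A single five-day count, taken at any point in a baseline period of about three years, carries seasonal error into the main exposure, and the article neither lists season as a variable nor acknowledges it. For completers the error is mainly non-differential and weakens the association in the first study question.

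The plausible loss in the log-step slope runs from about 2-3% (±10% swing) to 18-24% (±30% swing). This rests on an assumed between-person CV of 40-50%, a sinusoidal pattern common to all participants and testing spread evenly over the year. The documents can neither confirm nor exclude any value in that range.

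**What to change.** 1. **Adjust for date of wear.** Include the calendar date in every model with step count, as sine and cosine terms or as season. Enter steps on the log scale, so that a proportional seasonal swing becomes additive and the terms can absorb it. Cost: about two degrees of freedom and a sentence of analysis text. The wear dates should already be held with the monitor records and activity logs. This removes the average seasonal pattern, not individual departures from it.
2. **Standardise before cutting.** If steps are categorised, or given a threshold in the prediction tool, use season-standardised steps and state how a future user applies the standardisation. Cost: analysis wording.
3. **Name it.** Add season of wear to the limitations and qualify the Discussion's claim about how well the recording represents activity. Cost: one sentence.
4. **Optional, minor.** For any participants still to be tested, start the five counted days on the day after the visit. A Monday visit then gives one weekend day and a Tuesday-to-Friday visit gives two. The monitor comes back one day later. For records already collected, use the number of weekend days as a covariate, because a Monday-to-Friday record holds no weekend day to reweight. With an expected effect under 1%, this can be left out without much loss.

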### Fall incidence

Fall history of the participants are measured retrospectively as a 12-month recall of falls at baseline. Prospective falls are ascertained over a 12-month period by monthly phone calls with the purpose of determining both the number of falls, why the fall occurred, where it occurred, and when during the day the fall incidence happened. Falls are listed as number of falls and expressed in groups: fallers, non-fallers and multiple fallers along with fall rate per person in a year. This is in accordance with international recommendations [﻿84﻿].

### Socio-demographic data

The socio-demographic data describing age, gender, marital status, type of dwelling, use of mobility devices, and use of home-care are collected. These data are registered at baseline through a self-reported questionnaire. Weight and height are measured objectively, using the Tanita Digital Scale for weight measured in kilograms and Tanita Leicester Height measure system for height measured in centimeters. All measures are approximated to the next integer.

### Health information

Health information including chronic disease, the number of prescribed medication and daily fluid intake are likewise registered at baseline through a self-reported questionnaire. The question concerning chronic disease is two-item (i.e., yes or no response possibility) with the possibility to specify the diagnoses. The question concerning the use of prescription medication is also two-item (i.e., yes or no response possibility, and if yes, the number of medications). Over the counter medicines are not accounted for in this study. Daily fluid intake (i.e., water, soft drink, coffee, tee, juice, milk and fruit syrup) is five-item (i.e., 0-½, ½-1, 1–1½, 1½-2, and > 2 l response possibility).

